## Abstract

**Background:**

Preventive nebulization of mucolytic agents and bronchodilating drugs is a strategy aimed at the prevention of sputum plugging, and therefore atelectasis and pneumonia, in intubated and ventilated intensive care unit (ICU) patients. The present trial aims to compare a strategy using the preventive nebulization of acetylcysteine and salbutamol with nebulization on indication in intubated and ventilated ICU patients.

**Methods/Design:**

The preventive nebulization of mucolytic agents and bronchodilating drugs in invasively ventilated intensive care unit patients (NEBULAE) trial is a national multicenter open-label, two-armed, randomized controlled non-inferiority trial in the Netherlands. Nine hundred and fifty intubated and ventilated ICU patients with an anticipated duration of invasive ventilation of more than 24 hours will be randomly assigned to receive either a strategy consisting of preventive nebulization of acetylcysteine and salbutamol or a strategy consisting of nebulization of acetylcysteine and/or salbutamol on indication. The primary endpoint is the number of ventilator-free days and surviving on day 28. Secondary endpoints include ICU and hospital length of stay, ICU and hospital mortality, the occurrence of predefined pulmonary complications (acute respiratory distress syndrome, pneumonia, large atelectasis and pneumothorax), and the occurrence of predefined side effects of the intervention. Related healthcare costs will be estimated in a cost-benefit and budget-impact analysis.

**Discussion:**

The NEBULAE trial is the first randomized controlled trial powered to investigate whether preventive nebulization of acetylcysteine and salbutamol shortens the duration of ventilation in critically ill patients.

**Trial registration:**

NCT02159196, registered on 6 June 2014.

**Electronic supplementary material:**

The online version of this article (doi:10.1186/s13063-015-0865-0) contains supplementary material, which is available to authorized users.

## Background

Preventive nebulization of mucolytic agents and bronchodilating drugs is a strategy aimed at the prevention of airway obstruction in intubated and ventilated intensive care unit (ICU) patients [1–3]. This strategy was introduced in the 1990s [1, 2, 4], when it was recognized that invasively ventilated ICU patients are frequently unable to cough adequately, potentially resulting in stasis of sputum in the larger and smaller airways [5–7]. This could lead to clinically important atelectasis [8] and ventilator-associated pneumonia [9]. Preventive nebulization of mucolytic agents like acetylcysteine could, at least in part, solve this problem. As nebulization would dilute pulmonary secretions [10], it might be easier for a patient to evacuate secretions to the larger airways ready to be suctioned. As local application of acetylcysteine induces bronchospasm, traditionally a bronchodilating drug was added [1, 2, 11], with the additional advantage that bronchodilators like salbutamol augment mucociliary clearance [7].

Practices of nebulization during mechanical ventilation are known to be diverse, as evidence of a beneficial effect is limited and inconclusive [1, 2, 4, 12, 13]. In addition, care for the invasively ventilated ICU patient has changed significantly over the last decades. The commonly used practice of (deep) hypno-sedation and paralysis has been replaced by analgo-sedation with the restricted use of neuromuscular blocking agents [14], and ventilated ICU patients are mobilized more frequently and early during the course of their disease [15]. These changes in care may have resulted in an increased ability of invasively ventilated ICU patients to clear their airways. Consequently, this may render preventive nebulization of mucolytic agents and bronchodilating drugs an ineffective and unneeded strategy during mechanical ventilation. This may be especially true because nebulization of mucolytic agents and bronchodilating drugs carries the risk of local and systemic side effects, such as acetylcysteine-induced bronchoconstriction [1, 16, 17], and salbutamol-induced tachycardia and tachy-arrhythmias [18–20]. Also, nebulization could temporarily hamper triggering of the ventilator by a patient, potentially causing hypoventilation and patient distress [21].

The aim of the present trial is to determine the efficacy and safety of a strategy using preventive nebulization of acetylcysteine and salbutamol compared to a strategy using nebulization on indication in intubated and ventilated ICU patients. Furthermore, the related healthcare costs of this preventive strategy are determined. We hypothesize that a strategy using nebulization on indication in invasively ventilated ICU patients is not inferior with regard to the number of ventilator-free days and survival to day 28, but is associated with fewer side effects and lower health-related costs, compared to a strategy using preventive nebulization.

## Methods/Design

### Design

This randomized controlled trial investigating the (cost-) effectiveness and safety of preventive nebulization of mucolytic agents and bronchodilating drugs in intubated and ventilated ICU patients, called the NEBULAE trial, is an investigator-initiated, national, multicenter, randomized controlled, open-label, two-armed non-inferiority trial in invasively ventilated patients admitted to participating ICUs in the Netherlands.

### Trial approval and conduct

The trial is conducted according to the principles of the Declaration of Helsinki as stated in the current version of Fortaleza, Brazil, October 2013 [22], the Dutch law of Medical Research Involving Human Subjects (WMO) and Good Clinical Practice Guidelines (GCP). The trial protocol is approved by the Institutional Review Board of the Academic Medical Center, Amsterdam, The Netherlands and reviewed for local feasibility by the Institutional Review Boards of all participating medical centers represented in Additional file 1. The trial is registered at www.clinicaltrials.gov (NCT02159196) and at www.trialregister.nl (NTR4465). The trial is supported in full by a peer-reviewed grant from ZonMW, Netherlands Organization for Health Research and Development [23], which provided constructive comments on the trial design. ZonMW is not involved in the process of data collection, data analysis, data interpretation, and writing of the report. Written informed consent has to be given by the patient or their legal representative before any trial related procedure is performed. The trial will be reported according to the Consolidated Standards of Reporting Trials (CONSORT) guidelines [24].

### CONSORT diagram

The CONSORT [25] diagram of the NEBULAE trial is presented in Fig. 1. Screening of consecutive patients admitted to one of the participating ICUs to verify the source population and conformance with enrolment criteria will be performed by the local investigators in all participating centers. The trial plan is to include 950 patients. If patients are excluded from participation, the reason(s) for exclusion are registered.

**Fig. 1 Fig1:**
[figure not shown]
Consolidated Standards of Reporting Trials (CONSORT) diagram. *Until successful extubation; ** From day 1 until extubation, death or day 28 if still intubated, whichever comes first; ^1^Including all patients as originally allocated after randomization; ^2^Including only those patients who completed the treatment protocol as originally allocated

### Setting

The trial is performed in at least seven ICUs, one in a university-affiliated hospital (the Academic Medical Center, Amsterdam) and six in teaching hospitals (Rijnstate Hospital, Arnhem; Onze Lieve Vrouwe Gasthuis, Amsterdam; Amphia Hospital, Breda, Oosterhout and Ettenleur; Antonius Hospital, Nieuwegein; Medical Center Haaglanden, The Hague and Leidschendam; and Isala Hospital, Zwolle) in the Netherlands.

### Population

Invasively ventilated adult nonpregnant patients, aged ≥18 years, with an anticipated duration of ventilation of more than 24 hours, are eligible for participation. Patients are excluded if they received invasive ventilation in another ICU directly preceding the present ICU admission; ventilation during transport to the hospital, or ventilation started in the emergency room or in the operating theater is allowed though. In cases where the medical history necessitates the continuation of bronchodilators (for example, for chronic obstructive pulmonary disease or asthma) or in cases of a known allergy to the trial medication, the patient will be excluded from participation. Patients with neuromuscular diseases or complete spinal cord lesions, and consequently with an expected need for long-term ventilation, are also excluded. Finally, previous randomization in the NEBULAE trial excludes patients from participation as well.

### Patient enrollment, randomization and blinding

Consecutive patients are screened for eligibility by local investigators and treating physicians. Patients meeting all inclusion criteria and no exclusion criteria are candidates for inclusion in the study and will be randomly assigned in a 1 to 1 ratio, after informed consent is given by the patient or their legal representative, to either a strategy of preventive nebulization of acetylcysteine and salbutamol four times daily (the ‘preventive nebulization’ arm) or nebulization of acetylcysteine or salbutamol on indication (the ‘nebulization on indication’ arm). Randomization will be performed by the local investigators and treating physicians as soon as possible, but always within 24 hours after start of invasive ventilation in the ICU. To avoid prediction of future patients’ allocation, randomization sequence is generated using a permuted block design with random block sizes stratified by study center. Maintenance of allocation concealment will be warranted using a central, dedicated, password-protected, SSL-encrypted web-based, automated randomization system, available 24 hours per day (ALEA® software, TenALEA consortium, Amsterdam, The Netherlands), developed by the Clinical Research Unit in the Academic Medical Center, Amsterdam, The Netherlands, which is not involved in the conduct of the study. Due to the nature of the intervention, blinding of the patients and caregivers is not possible. Outcomes assessment will be performed according to the study protocol by independent ICU physicians not involved in the trial. Investigators performing analysis are blinded for the intervention.

The assigned strategy is continued until tracheal extubation. If a patient requires reintubation and additional invasive ventilation within a period of 28 days, the strategy to which the patient is randomized will be resumed.

### Interventions

When randomized to the preventive nebulization arm, the patient will receive nebulization every 6 hours with solutions containing 300 mg acetylcysteine *plus* 2.5 mg salbutamol. Flasks of acetylcysteine and salbutamol are provided by the pharmacy of the participating center. Since no placebo will be used, labeling of the drugs is not necessary. Solutions are nebulized using jet nebulizers or vibrating mesh nebulizers, depending on local availability in the participating centers. Nebulizers are set according to manufacturer’s recommendations. External nebulizers are powered by pressured air or oxygen at a continuous flow of 3 to 5 L/min. The nebulizer will be attached to the tubing system, always after the heated humidifier or the heat and moisture exchange (HME) filter (that is, at the side of the patient). A nebulization session typically lasts 20 to 30 minutes. The type of nebulizer used will be recorded in the case record form (CRF).

When randomized to the nebulization on indication arm, nebulization of acetylcysteine *or* salbutamol is restricted. The doctor staff can decide to order nebulization of solutions containing 300 mg acetylcysteine *or* 2.5 mg salbutamol in case a patient has persistent thick and tenacious secretions [26] or in cases of bronchospasm (suspected when there is a clinical wheezing, and signs of obstruction of the lower airways on ventilator waves or the end-tidal CO_2_ curve), respectively. Daily reassessment of the indications mentioned above will reassure that nebulization is stopped when no longer needed. The decision to start and stop nebulization is recorded in the CRF.

### Concomitant medications

Mucolytic agents or bronchodilating drugs other than acetylcysteine and salbutamol are not used. Nebulization of drugs other than mucolytic agents or bronchodilating drugs (for example, antimicrobial and antimycotic agents, or ilomedine and iloprost) however, remains possible. They should be administered separately from the nebulization of acetylcysteine and salbutamol and recorded in the CRF.

### Standard lung protective care

Standard care follows the local clinical guidelines and is performed by independent ICU physicians and nurses not involved in the trial. Doctor and nursing staff are encouraged to use lung-protective ventilation strategies, including the use of lower tidal volumes; restrictive sedation; early weaning, preferably by the use of weaning trials; fluid restriction; and infection prevention.

Lung-protection includes the use of lower tidal volumes (6 ml/kg predicted body weight, in patients with ARDS [27, 28], as well as in patients without ARDS [29]); higher levels of positive end-expiratory pressures (>5 cm H_2_O) are only used in cases of suspected shunting or signs of moderate or severe ARDS [30, 31].

Restrictive sedation includes the use of a local sedation guideline aiming at analgo-sedation and preventing hypno-sedation [32, 33], with a preference for intermittent sedation over continuous infusion of sedatives [34]; sedation depth is evaluated at least three times a day using the Richmond Agitation Sedation Scale (RASS) [35, 36]; pain is scored using the Numeric Rating Scale (NRS), Visual Analog Scale (VAS), Critical Care Pain Observation Tool (CCPOT) or Behavioral Pain Scale (BPS), and treated accordingly [37–39]. Delirium is assessed at least three times daily using a standardized tool, that is, the Confusion Assessment Method for the ICU (CAM-ICU) or the Intensive Care Delirium Checklist Screening (ICDCS) [40].

Doctor and nursing staff are encouraged to frequently test whether a patient triggers the ventilator and, if so, to use spontaneous modes of ventilation. Readiness to wean will be assessed on a daily basis. Pressure–support level is lowered stepwise to 5 cm H_2_O, as soon as patients are ready to be weaned from the ventilator. Attending physicians will decide to extubate the patient, based on general extubation criteria (for example, patient is responsive and cooperative with an adequate cough reflex, an adequate oxygenation saturation (>90 %) with PaO2/FiO2 of >200 mmHg and FiO2 ≤40 % and a respiratory rate of 8 to 30 per minute with no signs of respiratory distress (that is, marked accessory muscle use, abdominal paradox, diaphoresis, or marked dyspnea), is hemodynamically stable with no uncontrolled arrhythmia, and has a rectal temperature >36.0°C).

Fluid management follows the local guidelines and is dictated by clinical needs but aims at a neutral fluid balance as soon as possible after stabilization and weaning of inotropes and/or vasopressors [41]. Crystalloid infusions are favored over colloid infusions [42]. Transfusion of blood products is restricted.

Infection prevention consists of oral care, combining tooth brushing and rinsing of the oral cavity every 6 hours, and selective oropharyngeal decontamination or selective decontamination of the digestive tract are applied to all patients according to local clinical guidelines to prevent nosocomial infections [43]. Head-of-bed elevation is pursued [44]. Ventilator circuits are not changed routinely unless a circuit is visibly contaminated or damaged [45].

### Standard airway care

Independent ICU physicians and nurses not involved in the trial perform standard airway care, including endotracheal suctioning, humidification of inhaled air and tracheostomy placement.

Endotracheal suction is performed when clinically indicated and according to the local guidelines [46]. Normal saline instillation prior to endotracheal suction will not be used [46]. The use of an open or closed endotracheal suction system is left to the discretion of the participating center and will be recorded in the CRF.

Humidification and heating method of the inhaled air is left to the discretion of the participating center and will be recorded in the CRF. Active humidification of the air inhaled will be supplied by the use of an electrically powered humidifier. Passive humidification of the air inhaled will be supplied by the use of a heat and moisture exchange filter.

Tracheostomy is considered on indications only and preferably not in the first ten days after intubation [47]. Indications for tracheostomy are failure to intubate, expected duration of ventilation >14 days, Glasgow Coma Score <7 and/or inadequate swallow or cough reflex with retention of sputum, severe ICU acquired weakness, prolonged or unsuccessful weaning and repeated respiratory failure after tracheal extubation.

### Primary outcome and secondary outcomes of the trial

The primary outcome of this study is the number of ventilator-free days (VFD) and survival to day 28, defined as the number of calendar days of unassisted breathing, after both ICU admission and start of mechanical ventilation to day 28, if the period of unassisted breathing lasted at least 24 consecutive hours. Unassisted breathing is defined as being extubated, ventilating with or without facemask, nasal prong oxygen, room air or tracheostomy breathing, but always without continuous positive airway pressure or pressure support of intermittent mandatory ventilation assistance. Patients who die before 28 days or are mechanically ventilated longer than 28 days are assigned zero ventilator-free days.

Secondary outcomes include clinical endpoints and cost-effectiveness outcomes. Clinical endpoints include the following: ICU and hospital length of stay (LOS); ICU, hospital, and 90-day mortality; development of moderate or severe ARDS; ventilator-associated pneumonia (VAP); development of atelectasis and pneumothorax; incidence of obstruction of the endotracheal tube (wherefore endotracheal tube exchange is indispensable); cumulative dose and duration of sedatives, cumulative dose and duration of neuromuscular blocking agents, development of delirium and incidence of side effects of nebulization of acetylcysteine and/or salbutamol. In addition, related healthcare costs will be compared from a health systems perspective over the time horizon of the trial and include direct medical and indirect costs of days of mechanical ventilation, stay in the ICU and hospital, cumulative use of sedatives and neuromuscular blocking agents, tracheostomies and ventilator-associated pneumonia.

### Clinical data to be collected

Data on baseline, demographic characteristics and disease severity are collected on the day of enrolment, including gender, age, height, weight, reason for ICU admission, reason for invasive mechanical ventilation and the APACHE II score. Furthermore, data are collected on the medical history including presence of diabetes mellitus, severe heart failure (New York Heart Association NYHA classification) [48], acute coronary syndrome or pulmonary disease, pulmonary or hematological malignancies, previous pulmonary radiation and/or surgery, and current use of immunosuppressive medication.

Data on clinical outcomes are collected on a daily basis up to day 28, discharge of the ICU or death, including data on duration of ventilation, length of stay in ICU and hospital. Location of the patient (ICU, hospital, other facility, or home) and life status (alive or deceased) is assessed on days 28 and 90.

Clinical data are collected on a daily basis up to day 28, discharge from the ICU or death, and these data include: intubation status (if extubated: time of extubation), tracheostomy status, mechanical ventilation parameters (see below), development of pulmonary complications (moderate or severe ARDS, pneumonia, atelectasis and pneumothorax); cumulative use and duration of sedatives and neuromuscular blocking agents; sedation score using the Richmond Agitation Sedation Scale (RASS) [35, 36]; level of pain (Numeric Rating Scale or Visual Analog Scale or Critical Care Pain Observation Tool or Behavioral Pain Scale) [37–39]; delirium score with the Confusion Assessment Method for ICU (CAM-ICU) or Intensive Care Delirium Checklist Screening (ICDCS) [40] score; amount and type of infused blood products; cumulative fluid balance and Sequential Organ Failure Assessment (SOFA) [49].

Parameters of mechanical ventilation are collected 1 hour after intubation and every day at a fixed time point up until extubation, day 28 or death including the following: tidal volume, respiratory rate, levels of PEEP, Ppeak and/or Pplateau, the level of pressure support, inspiration to expiration ratio, oxygen fraction of inspired air, minute volume and pulmonary compliance. The Lung Injury Score [50] and Oxygenation Index [51] are calculated.

Compliance data are collected on a daily basis until extubation up to day 28 or death, including the quantity of secretions, type of humidifier (active or passive), amount and indication of nebulization of acetylcysteine and/or salbutamol, episodes of nebulization of other agents and side effects of nebulization of acetylcysteïne and/or salbutamol.

Resource-use parameters and unit prices are collected to estimate healthcare costs from a health systems perspective and include the medical costs of ventilation, ICU stay, in hospital stay, cumulative use of sedatives and neuromuscular blocking agents, tracheostomies and ventilator-associated pneumonia.

### Sample size calculation

Randomized trials assessing the efficacy of preventive nebulization are absent, which hampered power calculations. Therefore, the sample size calculation, based on a non-inferiority design, is calculated using the mean duration of invasive ventilation and the associated coefficient of variation, respectively 5 and 0.7 (log-transformed data) days [52], with a noninferiority margin of 10 %. A maximum difference in clinical effectiveness of 10 % between the ‘nebulization on indication’ arm as compared to the ‘preventive nebulization’ arm will be tolerated to consider a strategy of ‘nebulization on indication’ not to be inferior, with regard to the primary endpoint ventilator free days. Using these assumptions associated with the study design, a one-sided type I error of 0.05 and 80 % power (type II error), yields a sample size of 950 patients, which includes a 5 % anticipated drop out.

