## Discussion

Mechanical ventilation is associated with an impaired clearance and retention of airway secretions, which can lead to airway obstruction, atelectasis, bacterial colonization and pulmonary infection [2, 7, 54]. Preventive nebulization of mucolytic agents and bronchodilating drugs is a strategy suggested to prevent these complications [2, 4, 7]. No previous studies have addressed whether this preventive strategy is effective in a general ICU population of intubated and ventilated ICU patients.

NEBULAE is the first randomized controlled trial sufficiently powered to investigate the effectiveness, safety and costs of preventive nebulization of mucolytic agents and bronchodilating drugs compared to nebulization on indication.

All patients with an expected duration of ventilation of more than 24 hours are eligible for inclusion. Patients are excluded if they are admitted and invasively ventilated in another hospital before admission to be able to determine the total duration of ventilation and guarantee recording of all episodes of nebulization.

A concern regarding safety could be the occurrence of endotracheal tube occlusion, although nebulization of acetylcysteine is allowed in both groups in case of thick and tenacious pulmonary secretions. Furthermore, nebulization of liquids and solutions may cause obstruction and malfunction of the expiratory valve due to deposition of the aerosolized medication. To minimize this risk, awareness and training about this risk among nurses and physicians is advocated. Thereby, filters will be used and changed daily to protect the ventilator. An interim analysis on safety will be performed to evaluate these concerns. Furthermore, sedation practice could mask potential patient discomfort caused by the intervention. Similar sedation aims in both arms of the trial need to be persuaded.

The main strength of this study is the potential generalizability of its findings, considering the participation of different types of ICU’s in several hospitals as well as the broad spectrum of patients being eligible for participation. Besides the intervention under study, which is a well-known procedure familiar to nurses and physicians in all participating centers, no additional measurements or procedures are part of the study protocol. Therefore, execution of the study is straightforward and feasible.

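### The 950 patients and 80% power are derived from log duration of ventilation, but the margin and the test are on 28-day ventilator-free days, so the 80% is not shown for the primary comparison

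*Protocol article*

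**What the plan says.** Under Sample size calculation, the Protocol article states that the size "is calculated using the mean duration of invasive ventilation and the associated coefficient of variation, respectively 5 and 0.7 (log-transformed data) days", "with a noninferiority margin of 10"%. The same paragraph says that this 10% is the largest tolerated loss of clinical effectiveness in the on-indication arm, "with regard to the primary endpoint ventilator free days". With "a one-sided type I error of 0.05", 80% power and 5% drop-out, it arrives at 950 patients.

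The section on primary and secondary outcomes defines the endpoint as ventilator-free days and survival to day 28, and adds: "Patients who die before 28 days or are mechanically ventilated longer than 28 days are assigned zero ventilator-free days". Data analysis makes the between-arm comparison of that endpoint the main analysis.

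Two further passages rely on the power statement. The Discussion part of the Abstract describes the trial as "powered to investigate whether preventive nebulization of acetylcysteine and salbutamol shortens the duration of ventilation". The main Discussion says: "NEBULAE is the first randomized controlled trial sufficiently powered to investigate the effectiveness, safety and costs".

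**The concern.** Duration of ventilation and VFD-28 are different variables. Duration is positive and skewed, and a log-normal model with a ratio margin suits it. VFD-28 has exact zeros for deaths and for patients still ventilated at day 28, so it cannot be log-transformed as it stands. Its spread depends largely on how many patients die, and mortality is not among the listed planning inputs. A 10% margin also means something different on each scale.

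The consequence is that a reader cannot tell what power the primary comparison has, or how many ventilator-free days may be lost before non-inferiority is rejected. The wider claims of adequate power rest on the same figure.

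**Working it through.** **1. Reproduce 950.**
Inputs from Sample size calculation: CV 0.7 on a log-normal duration, 10% margin, one-sided alpha 0.05, power 80%, 5% drop-out. Allocation is 1:1 (section on enrollment and randomization). Assumption: no true difference between arms.

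- SD of log duration = sqrt(ln(1 + 0.7²)) = sqrt(ln 1.49) = 0.6315
- Margin as a ratio of 0.9: −ln(0.9) = 0.1054
- (1.645 + 0.842)² = 6.18
- n per arm = 2 × 6.18 × 0.6315² / 0.1054², about 445 (unrounded inputs, rounded up)
- Total 890; 890 / 0.95 = 937, against 950 stated
- With 950 × 0.95 / 2, about 451 per arm: 0.1054 / (0.6315 × sqrt(2/451)) − 1.645 = 0.86, so power is 80.5%

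The stated inputs thus yield the stated size as a test on log duration. Nothing about VFD enters.

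**2. Power for the primary endpoint at the same size.**
The article gives no 28-day mortality and no VFD mean or SD, so these must be assumed:

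- duration D is log-normal with mean 5 days and CV 0.7, as in the plan;
- VFD = max(28 − D rounded up to whole days, 0) for survivors, and 0 for deaths;
- death is independent of duration;
- the test compares means by normal approximation, one-sided 0.05, 451 per arm, no true difference;
- the margin is 10% of mean VFD.

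With no deaths, simulation gives a VFD mean of 22.51 and SD of 3.45. With mortality q:

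- mean = (1 − q) × 22.51
- variance = (1 − q) × 3.45² + q(1 − q) × 22.51²
- power = Φ(margin / (SD × sqrt(2/451)) − 1.645)

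Example at q = 0.25: mean = 16.9; variance = 0.75 × 11.90 + 0.1875 × 506.7 = 103.9, SD 10.19; margin 1.69; 1.69 / (10.19 × 0.0666) − 1.645 = 0.84, power 80%.

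| Assumed 28-day mortality | Mean VFD | SD | 10% margin (days) | Power, 451 per arm |
|---|---|---|---|---|
| 15% | 19.1 | 8.65 | 1.91 | 95% |
| 20% | 18.0 | 9.52 | 1.80 | 88% |
| 25% | 16.9 | 10.19 | 1.69 | 80% |
| 30% | 15.8 | 10.71 | 1.57 | 71% |
| 35% | 14.6 | 11.08 | 1.46 | 63% |

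The SD rises from 3.45 without deaths to 11.08 at 35% mortality, while a margin defined as 10% of the mean shrinks from 1.91 to 1.46 days between 15% and 35%. Both effects lower power. If 5 days is taken as the median duration instead of the mean, the powers are 94%, 87%, 78%, 70% and 62%.

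**3. The wider claims.**
The Background hypothesis and the sample size section both concern non-inferiority of nebulization on indication. No calculation is given for a benefit of preventive nebulization, for safety outcomes or for costs.

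**The case against.** The best defence is that trials of preventive nebulization were lacking, as the article says, so duration was a natural planning variable. The paragraph ties the 10% to ventilator-free days, so a margin is given on the right endpoint, if not in days. On that plain reading the design can be adequate: at 25% mortality the model needs 902 evaluable patients, or 950 with drop-out, exactly the planned number. A fuller protocol or analysis plan may give the margin in days. All of this stands, and it limits the point. It does not turn a figure computed for log duration into the power of the VFD comparison.

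Four stronger readings are tempting, and the article does not support them.

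- *The trial is underpowered.* Power falls below 80% only if mortality exceeds about 25%, and the article states no mortality.
- *The margin is 10% of the 5-day mean duration, carried over to VFD.* The text applies the 10% to ventilator-free days. A half-day margin would be the reader's construction.
- *The ratio 0.9 points the wrong way.* On the log scale, a ratio of 0.9 for preventive over on-indication is the same as on-indication ventilation lasting up to 1/0.9 = 1.11 times as long. Choosing that over 1.10 is a convention.
- *Deaths were left out of the planning data.* The article lists no mortality input, but does not say how the cited data treated deaths.

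The modelled powers are also only indicative. General statistical considerations allows a Mann–Whitney test for non-normal data, and death may be related to duration.

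**Conclusion.** The point holds as a mismatch between the planning variable and the primary endpoint. The arithmetic on the stated inputs is sound (937 against 950), but the resulting 80% is a property of a log-duration test and not of the VFD-28 comparison to which the article assigns it. Under the assumptions above, with the margin at 10% of mean VFD, power at the planned size runs from about 95% at 15% mortality to about 63% at 35%, crossing 80% near 25%. Adequacy therefore depends on a mortality that the article does not state. This should be fixed, because the article relies on the power figure and the non-inferiority decision needs a margin in days; it does not call the feasibility of the trial into question. The two claims of power for a shorter duration and for effectiveness, safety and costs go beyond what was sized.

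**What to change.** Before any unblinded comparison:

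1. State the non-inferiority margin as a number of ventilator-free days on the VFD-28 scale.
2. Replace the 80% statement with the power that about 902 evaluable patients give for the planned VFD-28 test at that margin, over a stated range of 28-day mortality and SD. Keep the log-duration calculation, if wanted, as the explanation of how 950 was chosen.
3. Reword the Abstract's discussion and the main Discussion so that power is claimed only for non-inferiority of nebulization on indication in VFD-28.

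The cost is wording and a short recalculation. No extra patients are needed. The drawback is that the restated power may be less favourable than 80%.
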